#### Vocal tasks for stress biomarkers

Six types of vocal tasks are developed to analyse voice recordings. On days 1, 5, 10 and 15 (figure 3, sixth prompt), two vocal tasks are implemented before and after the completion of a stress induction task to provide gold standards for detecting stress levels based on within-participant comparisons. We rely on two validated stressful tasks, including a timed (ie, 60 s) arithmetic task^68 69^ and a timed adapted version of the Stroop test.^50 70^ Due to the repetition of the same vocal task at a 60-s interval, it is important that these two tasks present low levels of habituation for the participant, which led to our choice to count down from 20 to 0 (task 1), and repeat PA-TA-KA as fast as possible for 10 s (task 2). The PA-TA-KA test was previously used to identify vocal biomarkers of neurological disorders,^71 72^ while counting is a common task for vocal biomarker identification.^50 51 73^ The other four types of vocal tasks are used as stand-alone tasks, comprising structured and unstructured tasks, and consisting of reading aloud a predefined text,^73^,^75^ describing an image,^51 76^ the /a/ vowel phonation^73^ (ie, saying ‘ahhhh’ as long as possible in one single breath) and free speech.^75^ Regarding the reading aloud task, three texts with a neutral (ie, the human right declaration as reported elsewhere), happy and sad tone (excerpts from The Little Prince, a widely translated and familiar/accessible text) have been selected to last approximately 20 s each. Regarding the image description, in collaboration with a comic designer, three images representing daily scenes in Luxembourg–a park, a supermarket and a busy street – have been designed according to a set of guidelines for vocal biomarkers identifications (figure 4).^77^

**Figure 4 F4:**
[figure not shown]
Comic-style images of daily life situations, created for the picture description tasks. Participants are instructed to describe the image or parts of the image for at least 20 s.

#### Activity and social interactions

At each prompt and via a single-option question item, participants have to specify the type of activity they were engaged in (eg, work/study, transport, shopping, sport, leisure, household chores, family care, etc.), as well as to indicate via a checklist the people they are interacting with at that moment (eg, no one - I am alone, no one - but there are people around me, spouse or partner, child or children, other family member, friends, acquaintance or colleagues, other).

#### Perceived environment

At each prompt and via two multiple-option question items, participants report elements of their surrounding environment they are currently enjoying (eg, greenspaces, blue spaces, smells, sounds, building architecture, open space/view, weather), and the ones that are currently a problem to them (eg, noise, crowdedness, pollution, traffic, incivilities, building facades in poor condition, weather).

#### Mobility

GPS-derived variables include timestamp, longitude, latitude, number of satellites connected, altitude, precision, direction, activity, Horizontal Dilution of Precision (HDOP), Vertical Dilution of Precision (VDOP), Position Dilution of Precision (PDOP) and speed (figure 5A).

**Figure 5 F5:**
[figure not shown]
Example of FragMent mobility data (**A**) and transport and activity log (**B**). Participants are instructed to visualise, verify and complete their mobility and activity data every evening.

### Transport modes and location type

A transport and activity log is automatically created as the participant travels from one location to another. GPS-based algorithms automatically detect clusters of GPS points that are defined as stops and more dynamic segments that are defined as trips. For each trip segment, algorithms further classify a transport mode (eg, on foot, bicycle, motorised transportation mode, subway). This log is available to the participant at any time of the survey via a dedicated screen of the app (figure 5B) with the possibility to visualise, correct and complement the predicted transport mode by specifying their actual mode of transport, indicating the type of location visited (eg, home, work/study place, gastronomy, leisure, shopping, nature, family/friend’s place, etc.) and whether this activity location was performed inside or outside. As a reminder, participants are invited every evening to verify and complement their own mobility and activity data.

### Environmental exposure measurements and modelling

The regular, daily and momentary environmental contexts will be assessed objectively using environmental indicators derived from a Geographic Information System (GIS). Environmental indicators will relate to the socio-demographic, built and natural environments. Regular destinations reported with the map-based questionnaire and GPS data collected through the FragMent app will be enriched with the GIS data. Exposure will be measured using standard circular street network buffers of various sizes along the GPS tracks (eg, 50 m, 100 m and 200 m)^78^ as well as around regular destinations collected through the VERITAS map-based questionnaire (500 m, 800 m 1000 m), aiming at representing the relevant exposure areas to be tested in sensitivity analyses. Finally, time-weighted exposure measurements^79^ (ie, kernel density estimation models, density ranking and point overlay) accounting for time spent at different locations and during travel will be further investigated and compared with unweighted exposure models.

### Analytical approach and power analysis

#### Identification of vocal biomarkers of stress

Identification of vocal biomarkers of stress includes the following steps^51^: (i) audio preprocessing, including resampling, normalisation, noise reduction, framing and windowing the data; (ii) audio feature extraction using the library DisVoice (https://disvoice.readthedocs.io/en/latest/reference.html), including glottal, phonation, prosody, articulation and phonological features; (iii) audio feature selection (eg, selection of “explainable feature” such as mean and SD) and dimensionality reduction (eg, via principal component analysis) aimed at selecting the most relevant features for the prediction of stress; (iv) automatic classification of stress based on machine learning algorithms (eg, XGBoost, Support Vector Machine); and (v) computation of performance metrics including accuracy, specificity and sensitivity metrics. In order to avoid systematic bias toward minorities (groups under-represented in the dataset) in the ability to accurately classify stress, algorithms have been pretrained on the Colive Voice dataset, an international and anonymous cohort aiming at detecting vocal biomarker candidates of numerous health outcomes based on vocal tasks from participants located worldwide.^73 74 80^

#### Relationships of environmental exposure and activity patterns, with momentary, daily and chronic stress

Multivariate adjusted models will be used to test the association between regular exposure patterns, regular activity patterns and chronic stress. Multilevel mixed adjusted models will be used to account for the repeated sampling design (eg, multiple measurements per participant) in the association between momentary/daily environmental exposures, activity patterns and momentary/daily stress. Social inequalities in stress will be examined by adding interaction terms to test the moderating effect of gender and socio-economic status on the relationships between exposure patterns, activity patterns and stress. Specific attention will be paid to minimise potential residential self-selection bias^81^ (ie, by controlling for individual preferences people had when moving in their residential neighbourhood) and selective daily mobility bias^82 83^ (ie, by considering truncated activity spaces measures, comparing actual path between locations to the shortest path, etc.). As our sample may deviate from the general population, we will use survey weights.

#### Power analysis

The following elements were considered to calculate the sample size. First, an estimated 10% of the participants completing the survey is expected to engage in the mobile survey (full option).^78^ A minimum of 200 participants is needed to ensure sufficient variability in terms of demographics and feasibility of the moderation analyses by social groups. Second, participants are followed over 15 days to ensure observing sufficient potential within-person variability. Third, a high power is needed to account for variability in effect size by environmental factor. Fourth, four to six micro-questionnaires per day will be sent to participants. A completion rate of 66% is expected.^62^ Given these considerations, Monte Carlo simulations were conducted using the R package SIMR^84^ to determine the power of an analysis with the following characteristics: a generalised linear mixed model for a binomial outcome (‘high stress’ vs ‘low stress’) with 17% of observations estimated to be ‘high stress’^28^; a continuous, within-person varying predictor, a+2% expected change in high-stress prevalence related to an increase of one SD in the predictor^14^ and two random effects controlling for the nested structure of the data (ie, repeated measurements per individuals, themselves nested by municipality of residence. After 1000 simulations, the results indicated a power of 99.80% (95% CI: 99.28, 99.98). Despite the very high estimated power, the number of participants will be maintained at 200 for the reasons stated above.

While the sample size of 200 participants was determined through power analysis, previous studies with similar designs have successfully drawn comparisons between demographic groups using sample sizes ranging from 100 to 250 participants.^17 85^ These studies included neighbourhood-level comparisons and incorporated sociodemographic variables in their models. In our study, we further enhanced this approach by employing targeted recruitment strategies to ensure inclusion of underrepresented groups, aiming for variability in age, gender, socio-economic status and residential environment.

### Pilot study

The feasibility of the study has been evaluated in a pilot study (n=12), performed in three languages (ie, English, French and German). Participants were recruited via snowball sampling and had to comply with the study eligibility criteria. For practical reasons, only the first traditional web-based questionnaire and the 15-day GEMA survey were evaluated in this pilot phase. A description of the participants’ socio-demographics and stress levels is provided in table 2.

**Table 2 T2:** Descriptive statistics of the pilot sample (n=12)

	Percent (n)	Mean (SD)	Median	IQR
Age		42 (12.4)	41	21.5
Languages				
English	33 (4)			
French	42 (5)			
German	25 (3)			
Women	58 (7)			
Living alone	50 (6)			
Education level				
No Education to General secondary education	8 (1)			
Vocational or technical secondary education to Bachelor’s degree	8 (1)			
Bac+4 or equivalent to Doctorate	84 (10)			
Smartphone request to conduct the study	66 (8)			
Physiological quality of life (4-20)		14 (2.1)	15	2.1
Psychological quality of life (4-20)		15 (2.1)	15	3.7
Perceived chronic stress (0–40)		22 (7.6)	23	8.5

Overall, 12 participants answered 401 questionnaires over the 15-day period, among which 90% (361 questionnaires) were schedule-based and 10% (40 questionnaires) were event-based, triggered by the outdoor location of the participant. Out of a total expected number of 60 scheduled-based questionnaires, a participant answered on average 33.4 questionnaires, with a median of 13 days and a minimum of one answer per day. The distribution of the response rate over the day is similar in the morning, at noon, in the afternoon and in the evening (range: 49.4 %–50.5 %). Most of the answered prompts were filled within 45 min (84.3%) (ie, without reminders).

Regarding the vocal tasks, 81.8% of the vocal recordings were exploitable to analyse vocal biomarkers of stress, including clean (64.3%) and slightly noisy (17.5%) recordings. Empty (2.1%), noisy (11.7%), wrong task (0.5%), and other' (ie, people whispering, microphone covered, etc.) (3.9%) recordings will not be analysed.

Participants reported low to medium momentary stress levels (mean (sd)=25.2 (21.5)), which stayed stable over the last hour in 39.4% of cases, increased in 25.2% of the cases and decreased in 35.4% of the cases. Stressors identified in the evening via the adapted version of the Daily Inventory of Stressful Event (DISE) most frequently fell under *‘nothing stressful’* (47.2%), followed by stressors experimented in the *‘Work/study or work/study-related context’* in 29.2% of cases.

Regarding the perceived environment, participants identified no problems in their surrounding environment in most cases (79.8%), while they often enjoyed the open space/view (26.4%), the weather (24.2%) and the presence of greenspaces (19.5%). Most prompts were answered at work (27.9%), while resting (14.7%), eating (13.0%) or during leisure activities (12.7%). Finally, 61.3% of the prompted were answered while being alone, 15% in the company of a spouse/partner and 10% in the company of children. A complete description of participants’ responses is provided in table 3.

**Table 3 T3:** Descriptive statistics of the 15-day mobile survey

	Percent (n)	Mean (SD)	Median	IQR
Characteristics and adherence to the EMA survey design				
Pct. of answered EMA prompts by trigger (n=401)				
Schedule-based trigger	90.0 (361)			
Event-based (being outdoor) trigger	10.0 (40)			
Compliance rate of schedule-based prompts	50.1 (361)			
Nb. of answered EMA prompts per participant		33.4 (12.9)	25	23
Nb. of days with at least one answered EMA prompt per participant		12.4 (2.8)	13	2
Compliance rate of schedule-based EMA-prompt across the day				
Morning (08:00–09:00)	50.0 (90)			
Noon (12:000–13:00)	50.5 (91)			
Afternoon (16:00–17:00)	50.5 (91)			
Evening (20:00–21:00)	49.4 (89)			
Nb. of answered EMA prompts after reminder (45 min)	15.7 (60)			
Vocal tasks				
Compliance rate per vocal tasks				
All	50.0 (384)			
A Vowel phonation	52.4 (44)			
Free speech	50.0 (66)			
Image description	49.7 (113)			
Read-out-loud	50.5 (115)			
Count down	41.7 (20)			
PA-TA-KA task	54.2 (26)			
Quality of vocal recordings				
Clean	64.3 (247)			
Empty/silence	2.1 (8)			
Noisy	11.7 (45)			
Slight Noise	17.5 (67)			
Wrong task	0.5 (2)			
Other	3.9 (15)			
Stress and mood				
Momentary stress (0–100)		25.2 (21.5)	20	27
Stress evolution during the last hour				
Increased	25.2 (101)			
Not changed	39.4 (158)			
Decreased	35.4 (142)			
Mood (0–100)		71.2 (18.5)	71	38
Daily inventory of stressful events				
Your kid(s), partner or close friend	10.1 (9)			
A task you were performing	6.7 (6)			
While travelling	4.5 (4)			
Work/study or work/study-related context	29.2 (26)			
Home-related event	3.4 (3)			
Your health	4.5 (4)			
Other	4.5 (4)			
Nothing stressful	42.7 (38)			
Perceived environment, activities and social company				
Problems in the surrounding environment				
Noise (car, construction work, etc.)	7.0 (28)			
Crowdedness	2.2 (9)			
Pollution, smells	1.5 (6)			
Car traffic	4.2 (17)			
Feeling of insecurity (people, blind wall, lack of lighting, etc.)	0.3 (1)			
Physical decay (poorly maintained infrastructure, garbage, graffiti, etc.)	0 (0)			
Weather	8.7 (35)			
None of them	79.8 (320)			
Enjoyment of the surrounding environment				
Green spaces (park, forest, vegetation)	19.5 (78)			
Blue spaces (river, lake, fountain, waterbodies…)	0.8 (3)			
Smells	7.5 (30)			
Sounds	12.7 (51)			
Building architecture	6.0 (24)			
Open space, view	26.4 (106)			
Weather	24.2 (97)			
None of them	42.4 (170)			
Activities				
Work/study	27.9 (112)			
Transportation (car, train, bus, bicycle, walking…)	9.2 (37)			
Shopping	1.7 (7)			
Sports	3.2 (13)			
Leisure activities	12.7 (51)			
Household chores	8.5 (34)			
Family care activities	3.5 (14)			
Self-care activities	5.5 (22)			
Eating	13.0 (52)			
Rest	14.7 (59)			
Social company				
No one, I am alone	40.6 (163)			
No one, but there are people around me	20.7 (83)			
Spouse or partner	15.0 (60)			
Child or children	10.5 (42)			
Another member of your family	1.2 (5)			
Friends	8.2 (33)			
Acquaintance or colleagues	9.5 (38)			
Other	1.2 (5)			

After the completion of each survey, participants responded to feedback questions adapted from Eisele (2022)^86^ regarding perceived burden, ease of use, instructions, and careless responding, and provided additional feedback on their overall experience in open text sections (online supplemental table 1). Participants reported a moderate to high enjoyment of completing the survey, which was generally evaluated as rather easy to complete. Using the app was assessed as low to moderately stressful. The survey was evaluated as moderately tiring, irritating and disturbing of one’s everyday life. The vocal tasks were also moderately stressful and irritating, and participants reported a good to very good understanding of the instructions to perform the vocal tasks. The participants' perception of moderate support from the research team during the survey was addressed in the study by sending four encouragement e-mails over the 15-day monitoring period to help maintain their motivation and provide support when needed.

### Participant and public involvement

None.

## Discussion

FragMent is the first study combining the investigation of momentary, daily and chronic stress, measured objectively and subjectively, in relation to immediate, daily and regular exposures to environments, and activity patterns. While FragMent will advance existing knowledge on environmental determinants of stress, it departs from traditional neighbourhood and health studies by accounting for individual mobilities in exposure assessment in many conceptual and methodological ways.

The study examines the in-depth effects temporarily in neighbourhood effects on stress by disentangling exposure patterns into exposure durations, frequencies and temporal configuration over the course of the day (ie, sequences, temporal clusters, etc.).^42^ Notably, a better understanding of the effect of exposure temporalities in stress may translate into a better estimation of social inequalities in stress. Indeed, more vulnerable social groups may be exposed more frequently to stressful environments, spend more time therein and be less able to alternate sequences of exposures from stressful to more restorative environments. Not accounting for exposure temporality may thus result in a systematic misestimation of social inequalities in stress.

FragMent is the first study to combine a GEMA design with voice technology, considered today as one of the most promising sectors to identify symptoms in a non-invasive way,^51^ in order to detect biomarkers of stress. Observational or clinical studies embracing voice technology typically only include multiple recordings at one point in time or a single vocal recording prestressor and posttressor exposure. Compared with these studies, the repeated daily vocal sampling (four times per day) over 15 days of our study will produce a unique dataset (expected 7920–12000 vocal recordings), rich in multiple vocal tasks (eg, image description, text reading, etc.). FragMent vocal tasks further include the completion of four vocal tasks prestress and poststress induction tasks (ie, two arithmetic tasks and two Stroop tests). Although the level of difficulty of the tasks was not adjusted on the participant’s capabilities, this aimed to provide four gold standards over 15 days for detecting stress levels based on within-participant comparisons. Overall, the FragMent dataset will open up new opportunities for in-depth investigations of vocal stress biomarkers, including within and between participant variations thereof and tied to varying environmental contexts. Furthermore, the ecological nature of the recordings helps to better identify vocal biomarkers in real stressful situations, as compared with clinical studies relying on ‘artificial‘ stressors. Finally, to our knowledge, FragMent is the first study to investigate the effect of environmental stressors on vocal biomarkers.

The 15-day follow-up provides a unique opportunity to observe full variability in stress experiences and associated environmental exposures and activities across various spatial and time-related contexts (ie, weekends vs weekdays; mornings vs noon vs afternoons vs evenings). Indeed, a recent review of GEMA studies for establishing new reporting guidelines reported only 4 studies out of 20 with a longer monitoring period ranging from 30 to 60 days.^64^ The 15-day monitoring period further addresses the relative lack of accuracy in capturing participants’ full activity space in GPS studies below the recommended 2 weeks threshold.^87^

FragMent uses the latest technological developments in mobile sensing and EMA software to not only sample participants’ stress experiences in various time-related contexts, environments and activities but also specifically target their outdoor experiences by triggering questionnaires based on their location. While the outdoor triggering of questionnaires, based on GPS information (ie, number of satellites connected and precision indicators), may be sensitive to the proximity to large windows or to urban canyons, we believe that collecting information on environmental exposures via a window, rather than a proper outdoor exposure, would still provide valuable insights on the participant’s visible surrounding environment.

The Eco–Emo tracker GEMA application enables us to produce and investigate acute and innovative indicators of participants’ sequences of activities in relation to their stress levels by combining momentary questionnaires on activities and social context, continuous GPS tracking and associated time-stamp and automatically processed daily visualisations of the participants’ timelines of stops, trips and transport modes to be verified, corrected and completed by the participant. However, building accurate sequences of exposures and activities remains challenging due to signal loss, incomplete or unverified timeline data and response rate to daily questionnaires.

A further strength of FragMent is its fully automated survey process based on a prewritten study script embedded in the application. This enables a large-scale GEMA study with national coverage across a wide adult age range (18–65 years old), while requiring minimal technical and human resources. Despite its feasibility and scalability, the multisurvey components of FragMent with a 15-day follow-up come with challenges to foster high completion rates and to limit the attrition at each step of the survey period.

The pilot study registers a 50% compliance rate, which is acceptable compared with GEMA studies reporting between 50% to 100% compliance rates.^64^ However, the addition of vocal tasks precludes a full comparison with more traditional (G)EMA studies, as the nature of the vocal task itself implies the need to speak aloud on the phone, which may not always be perceived as feasible by the participant in every context. The mismatch between the compliance rate observed in the pilot study and the expected compliance rate considered in the power analysis (66%) may result in a lower analytical power. However, pilot studies should not be used to inform power calculation due to their limited samples,^88^ but should be used to evaluate the feasibility, which was confirmed here. Furthermore, the estimated power from 200 participants engaged in the mobile survey was very high (99.8%), indicating that foreseen analyses may not suffer from a slightly lower response rate. Finally, the survey design was improved after the pilot to maintain participant adherence to the protocol with encouraging e-mails sent over the monitoring period.

Regarding causal inference, the study has developed some questionnaire items and methods to control for confounding linked to residential self-selection and selective daily mobility. In addition, the 15-day GEMA design allows for the examination of micro-longitudinal within-person stress-environment associations. Notably, the study will be able to investigate temporal sequences with environmental exposures assessed prior in time to stress evaluation. With these approaches, we will attempt to improve as much as possible the quality of causal inference from our data.

Finally, the possibility that the mobile survey and associated vocal tasks are experienced as stressful by the participant cannot be ruled out. To cope with this bias, participants are asked to experience the typical survey questions and vocal tasks 24 hours before the start of the survey to reduce the effect of surprise linked to the first vocal recording. The 15-day data collection will further enable us to perform some sensitivity analyses by comparing the stress levels with and without the first one or 2 days of the survey, during which the participant may be more stressed to miss a questionnaire or perform a vocal recording.

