During the 15-day Ecological Momentary Assessment (EMA) phase, participants are prompted four to six times per day following recommendations on EMA protocol adherence.^62^ Four schedule-based prompts within a random component of 30 min are sent every 4 hours at 8 am, 12 pm, 4 pm and 8 pm to cover different activities, locations and environmental contexts.^14 63^ Each prompt is available for 1 hour and a reminder to complete the questionnaire is sent after 45 min. At each of the four schedule-based prompts, participants must complete a short questionnaire and a vocal task. Two additional prompts are event-based and conditionally triggered if participants are outdoors sometime between 09:30 am and 11:30, and between 17:30 and 19:30 to specifically collect data on the outdoor experience using a short questionnaire. The system detects the participant’s outdoor location using GPS information, including the number of satellites connected to the smartphone and precision indicators. No vocal tasks are requested on the event-based prompt to minimise outdoor noise interference. No reminders are sent for the event-based prompts, and their availability to the participants is limited to 30 min. The app continuously collects smartphone GPS-based locational data over 15 days, at a sampling rate of 5 s. Thanks to an automatic recognition of trips and stops, participants are further invited to fill in a transport and activity logs via the app. Both location data and answers to questionnaires are transmitted in real-time to the survey platform on servers exclusively located in Europe. During the 15-day monitoring period, the participants are kept informed of the ongoing collection of GPS and survey data by a permanent notification display about the data collection progress on their smartphone.

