#### Stress, stressful events and mood

Momentary stress is evaluated with one single item ‘how stressed are you now’, ranging from 0 (Not at all) to 100 (Very stressed).^66^ A second stress-related item assesses how the participant’s stress level has changed over the past hour, based on a 5-point Likert scale response option. Mood is evaluated with the Visual Analogue Mood Scale, ranging from 0 (Sad) to 100 (Happy).^62^ In the evening prompt, we use an adapted version of the Daily Inventory of Stressful Events^67^ as a checklist of potential stressors encountered during the day regarding seven contexts (eg, your kid(s), partner or close friend and work/study related context).

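### The day 1-2 sensitivity check for survey-caused stress cannot separate novelty from the day-1 stress induction and keeps three of four induction evenings; add handling of those evenings and of post-stressor recordings

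*Protocol article*

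**What the plan says.** The Discussion gives two responses to stress caused by the survey. One is a design measure: "participants are asked to experience the typical survey questions and vocal tasks 24 hours before the start of the survey". The other is an analysis: "comparing the stress levels with and without the first one or 2 days of the survey". The reason given for choosing those days is that they are a time "during which the participant may be more stressed to miss a questionnaire or perform a vocal recording". The inductions are not mentioned there.

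The section Vocal tasks for stress biomarkers sets the induction schedule: "On days 1, 5, 10 and 15 (figure 3, sixth prompt), two vocal tasks are implemented before and after" a timed arithmetic or Stroop-type task. The purpose is "to provide gold standards for detecting stress levels based on within-participant comparisons". The scheduled prompts "are sent every 4 hours at 8 am, 12 pm, 4 pm and 8 pm", with one conditional outdoor prompt in the morning and one in the early evening, so the sixth prompt of the day is the 8 pm one.

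That prompt also carries the core questions, which include current stress (0-100) and change over the past hour, and the day's stressor checklist: "In the evening prompt, we use an adapted version of the Daily Inventory of Stressful Events".

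The modelling section (Relationships of environmental exposure and activity patterns, with momentary, daily and chronic stress) enters momentary and daily stress into adjusted mixed models. It does not say how induction evenings are treated. The Discussion also says that the study will examine effects of environmental stressors on vocal biomarkers.

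**The concern.** A check that removes only the first one or two days is hard to read in either direction when a stressor is given on days 1, 5, 10 and 15.

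- If stress levels differ with and without the early days, novelty and the day-1 induction are both possible causes.
- If they do not differ, stress made by the survey is not ruled out, because days 5, 10 and 15 stay in both sets.

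Two outcomes are at stake. For self-report, evening ratings on induction days may reflect the stressor, if they are given after it. For voice, a recording made just after a stressor is meant to sound stressed wherever the participant is, so it carries induced stress into any model that relates surroundings to voice.

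**Working it through.** **Inputs.** 200 participants (Sampling and recruitment); 15 days with 4 scheduled prompts per day (Mobile survey); 66% expected completion and a +2-point effect on high-stress prevalence (Power analysis); inductions on days 1, 5, 10 and 15 (Vocal tasks); pilot recording counts and compliance, 12 participants (Table 3).

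**The article's own figure.** Expected recordings: 200 × 15 × 4 = 12000, and 12000 × 0.66 = 7920. This reproduces the stated range of 7920-12000 with one recording per scheduled prompt.

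**Induction evenings left after the check.**

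| Days dropped | Induction evenings / evenings | Induction prompts / scheduled prompts |
|---|---|---|
| none | 4/15 = 26.7% | 4/60 = 6.7% |
| day 1 | 3/14 = 21.4% | 3/56 = 5.4% |
| days 1-2 | 3/13 = 23.1% | 3/52 = 5.8% |

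Removing the four induction-evening prompts instead leaves 60 − 4 = 56 scheduled prompts and no induction evening.

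**Recordings.** Expected counts follow from received count ÷ compliance:

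- All tasks: 384/0.50 = 768, and 768/12 = 64 per participant.
- Countdown: 20/0.417 ≈ 48. PA-TA-KA: 26/0.542 ≈ 48. Together 96, and 96/12 = 8 per participant.
- Eight per participant fits one recording before and one after each of four inductions. The other 64 − 8 = 56 match the 60 − 4 scheduled prompts without an induction.
- Post-stressor share by design: 4/64 = 6.3%. Among those received in the pilot: (20 + 26)/384 = 12.0% from induction sessions, and half of these, 23/384 = 6.0%, are post-stressor if the pairs are complete.
- Evening recordings only: 15 + 4 = 19 per participant, of which 4/19 = 21.1% are post-stressor. After dropping days 1-2: 13 + 3 = 16, and 3/16 = 18.8%.

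**Illustration for self-report.** Assume that the rating follows the stressor and that high-stress prevalence at those prompts rises by r points. The article gives no value for r, so a range is shown. Evening prevalence rises by r × 4/15 with all days kept, or r × 3/13 with days 1-2 dropped.

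| r | Evening, all days | Evening, days 1-2 dropped | All scheduled prompts, all days (r × 4/60) |
|---|---|---|---|
| 5 | 1.3 | 1.2 | 0.3 |
| 10 | 2.7 | 2.3 | 0.7 |
| 20 | 5.3 | 4.6 | 1.3 |

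An evening shift of 2 points, the size of the effect powered for, needs r = 2 × 15/4 = 7.5 with all days kept, or 2 × 13/3 = 8.7 with days 1-2 dropped. These are shifts in evening prevalence, not biases in an exposure coefficient. If the rating comes before the stressor, the same-prompt shift is zero apart from anticipation.

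**The case against.** The case on the other side is substantial, and most of it stands.

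- The check is offered for novelty, not for induction, and is paired with a practice run. That stands: the check is incomplete rather than wrong in what it claims. It still mixes novelty with the day-1 induction.
- Which prompts and recordings enter which model is detail that a condensed article may leave to a fuller plan. That stands for the silence in the modelling section. It does not cover the interpretation of a sensitivity analysis that the article does specify.
- The induction recordings use their own two tasks and have a stated calibration role, so they can be identified. That stands, but a stated purpose is not an exclusion rule.
- The order of rating and stressor is unknown. The article lists the questionnaire before the vocal task, question order is randomised only among the questions, and Figure 3, which might settle the matter, is not available here. That stands, and it limits the self-report concern.
- The pilot feedback, "The vocal tasks were also moderately stressful and irritating", is an overall rating by 12 people. It does not show when the stress occurred. That stands, and no weight is placed on it.

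A reader might infer that stress produced by the app will be read as environmental stress. The documents do not support that. Induction days are fixed whatever the surroundings, so among evening prompts they are unrelated to exposure by design. The next scheduled prompt is about 12 hours later, and at most 4 of 60 scheduled prompts are involved. Distortion could enter mainly because evening settings differ from daytime ones, and adjustment for evening prompt or induction day would largely remove it.

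**Conclusion.** The point holds as a worthwhile, low-cost improvement, not as an error in the plan. The one analysis named for survey-caused stress leaves three of four induction evenings in the data and cannot isolate novelty on day 1.

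For self-reported stress, any effect depends on the rating following the stressor, which is not stated, and its effect on exposure estimates is not shown to be large. The voice outcome is the more direct risk. About 6% of recordings, and about a fifth of evening recordings, are post-stressor by design, whatever the order of the questions. This rests on two assumptions: that the pilot's recording structure (64 per participant, 8 from inductions) carries over to the main study, and that nothing in a fuller plan already excludes these recordings.

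**What to change.** 1. Keep the day 1-2 check. Beside it, add a sensitivity analysis that excludes the evening prompts of days 1, 5, 10 and 15, or flags them with an indicator. This covers the stress rating, the past-hour change item and the stressor checklist. With those evenings removed, the comparison with and without days 1-2 is no longer mixed with an induction.
2. State that post-induction recordings are used only to train and validate the classifier, and not as outcomes in models of environment on voice.
3. State whether the stress items come before or after the induction. Changing the order in the app is optional: it may already be questionnaire first, and data collection, planned to end in the third quarter of 2025, may be finished.

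The cost is a few sentences of analysis plan, at most 4 of 60 scheduled ratings per person in a sensitivity analysis, and about 6% of recordings in the voice-outcome analyses.
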